
#### Qualitative data analysis

Qualitative data will be thematically analysed by two research team members independently using a phenomenological inductive approach [61]. Transcripts will be returned to participants for comments/correction to ensure transparency and trustworthiness of the data (member checking) [69]. Validated transcripts will be read several times by two independent researchers to obtain an overall meaning. Then, themes and subthemes with important meanings common for all participants will be derived from the obtained data. Results will be compared through discussion between reviewers [70].

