#### Qualitative assessments

To understand participants’ experiences of taking part in the PAIL feasibility trial, focus groups will be conducted at mid-point (between the weeks 4 and 5) and at the end of the 12-week intervention using semi-structured discussions in small groups (four to nine people per group) of mixed gender (Additional files 5 and 6). The research team will check if any alterations will be required based on the participants’ feedback. The 32-item checklist for reporting qualitative research will guide the researcher to ensure clarity and transparency in focus groups methodology [59]. Focus groups will be audio recorded using a digital recorder and will be transcribed verbatim. An independent trained focus group leader will act as a moderator and facilitator of the focus groups [60].

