#### Feasibility outcomes

The following feasibility outcomes will be assessed in this study:Attendance will be calculated as the total number of attended sessions divided by the total number of sessions of the intervention and recorded as a percentage;Recruitment rate will be calculated as the number of individuals responding to advertisements and friends’ referrals out of a total number of formal invitations given/advertisements placed (including web-based advertisements, advertisements placed in the local cohort groups and poster and leaflet material disseminated in the community). Recruitment rate will be recorded as a percentage, e.g. 25% (48/195). It is acknowledged that advertisements may reach a large number of individuals but it is impossible to quantify this;Retention rate will be calculated as the number of participants completing the study as a proportion of those randomised;The appropriateness, practicality and acceptability of the designed intervention in the proposed settings will be assessed using focus group interviews. The focus group transcripts will be analysed using a phenomenological inductive approach [61], and these data will be used to help the research team to improve the quality of the delivered intervention by informing positive changes in the methodology and design of the intervention for the future implementation in a consequent study;The assessment rate of questionnaires will be evaluated as the total number of completed questionnaires divided by the total number of questionnaires and recorded as a percentage;The appropriateness of statistical methods of data analysis will be analysed by the research team in terms of suitability to the data;A power calculation and sample size estimation will be calculated for meaningful potential future primary outcomes (e.g. loneliness or social support) using a method based on the differences in means between the intervention and control groups, using the G-power software [62];The effect size (ES) will be calculated for loneliness, social support, social networks, anxiety and depression, self-efficacy for exercise, satisfaction with level of social contacts and the expected outcomes and barriers for exercise. Means (M) and standard deviations (SD) will be used to investigate the effect size for change in loneliness using mixed between (intervention group vs. control group) and within (over time) repeated-measures analysis of variance (ANOVAs) with post-hoc comparisons.

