### Data collection

Data will be collected at the university facility at screening, baseline and post-intervention period (12 weeks after the start of the intervention) (Fig. 1). After providing baseline eligibility screening, potential participants will be offered a total of five visits for health assessments at the university facility. Participants in the intervention group will have an additional sixth visit for attending the mid-point focus group. All digital data (transcripts, digital information, health assessment databases) will be stored securely on the password-protected university computers available only to the research team. All other data (e.g. eligibility screening forms, activity data and questionnaire data) will be pseudo-anonymised with a unique ID number and stored in locked filing cabinets/on password-protected university computers accessible only to the research team. Only the researchers will have access to the data.

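### The theme criterion in the qualitative analysis asks for meanings shared by everyone, so read as written it leaves out barriers voiced by only some participants (minor)

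*Protocol article*

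**What the plan says.** Three sections of the protocol article bear on this point.

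- **Feasibility outcomes** names the source of evidence: "The appropriateness, practicality and acceptability of the designed intervention in the proposed settings will be assessed using focus group interviews". No other listed outcome is described as a measure of these three properties. The same item says the transcripts will serve to improve the intervention and its design for a later study.
- **Qualitative assessments** sets the timing: "focus groups will be conducted at mid-point (between the weeks 4 and 5) and at the end of the 12-week intervention". The format is "semi-structured discussions in small groups (four to nine people per group) of mixed gender". It adds that "The research team will check if any alterations will be required based on the participants’ feedback".
- **Qualitative data analysis** sets the method: "Qualitative data will be thematically analysed by two research team members independently using a phenomenological inductive approach". Transcripts go back to participants for comment, two researchers read them, and then "themes and subthemes with important meanings common for all participants will be derived from the obtained data". The two sets of results are compared by discussion.

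Data collection links the mid-point group to one arm: "Participants in the intervention group will have an additional sixth visit for attending the mid-point focus group".

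**The concern.** Acceptability is among the primary aims listed in the Abstract, and focus groups are its one stated source of evidence. The only criterion the article gives for what becomes a theme is that its meaning is shared by everyone. A difficulty that some participants meet and others do not fails that criterion.

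A feasibility study needs to learn about such difficulties. The Feasibility outcomes section wants the data in order to improve the intervention. The Progression criteria section foresees changes to the intervention and a re-run if the criteria are not met. Both uses depend on knowing what troubled some participants, and a criterion of universal agreement suits that poorly. Attendance and retention are counted, but a count of who came and who stayed does not give reasons.

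**Working it through.** The article states no figure on this point, so there is none to reproduce. The check is mainly a comparison of passages, followed by a small illustration.

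**Comparison of passages**

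1. Source: the item on appropriateness, practicality and acceptability in Feasibility outcomes names focus groups and nothing else.
2. Purpose: the same item says the data are to improve the intervention.
3. Criterion: Qualitative data analysis derives themes and subthemes whose important meanings are shared by all participants. It states no step for divergent or minority views.
4. Safeguards in the same section: returning transcripts to participants checks their accuracy, and two independent readers check the analysts' agreement. Neither brings back a view that fails the criterion in step 3.
5. Other route: the feedback check in Qualitative assessments carries no condition of shared meaning. It also has no stated method, and it does not change what is reported as a theme.

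Steps 1 to 3 together mean that the single source for acceptability passes through a criterion that does not fit its stated purpose.

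**Illustration of how strict a literal reading is**

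Inputs from the article:

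- 20 participants per arm (Sample size).
- Retention threshold of 75% per group (Progression criteria), so 0.75 × 20 = 15.
- Focus groups of 4 to 9 people (Qualitative assessments).

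Assumptions: the prevalence p of a view is chosen for illustration, views are independent between people, and everyone counted attends.

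The probability that all n people hold the view is p^n:

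| p | n = 4 | n = 9 | n = 15 | n = 20 |
|---|---|---|---|---|
| 0.50 | 0.063 | 0.002 | <0.0001 | <0.0001 |
| 0.80 | 0.41 | 0.13 | 0.035 | 0.012 |
| 0.95 | 0.81 | 0.63 | 0.46 | 0.36 |

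For example, 0.80^15 = 0.035.

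The probability that at least one of n people holds the view is 1 − (1 − p)^n. For p = 0.20 this is 1 − 0.80^15 = 0.96 with n = 15, and 1 − 0.80^20 = 0.99 with n = 20.

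A difficulty felt by one person in five would therefore almost certainly be held by someone in the groups, yet would almost never be shared by all of them (0.20^4 = 0.0016 even within a single group of four). Taken across the arm, a literal criterion also drops most views held by a clear majority.

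**The case against.** The strongest reply is that the sentence is loose wording for the usual search for shared meaning under a phenomenological approach. The word *only* does not appear, and nothing says other content is discarded. The illustration supports this reply: a criterion that even an 80% view would rarely meet is hardly workable, so the authors may not have meant it literally. Feedback is also checked separately for needed alterations, and the Questionnaires section gives each participant a scale on barriers to exercise, which does not depend on group agreement.

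Much of this stands, and it is why the point is minor. It does not remove the point. The wording is the only theme criterion stated, so an analyst who follows it has no stated basis for reporting a minority view as a theme. The barriers scale concerns habitual exercise, and the article does not name it as a measure of this intervention's acceptability. Nor can the condensed form of a journal article explain the wording, because the criterion is stated, not left out.

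A reader might infer more than the article supports:

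- *That people who left or declined are excluded by the criterion.* It acts on whatever transcripts exist and excludes nobody. Who is invited to the final groups, and whether reasons for refusal or withdrawal are recorded, are details a condensed article may leave to the full protocol. People who leave later could also be heard at weeks 4 to 5.
- *That the criterion biases the result towards acceptable.* A literal criterion would equally drop favourable views that are not unanimous, so no direction is shown.
- *That willingness to participate has no measure beyond the focus groups.* Recruitment, attendance and retention are listed outcomes and give behavioural evidence on it, though not reasons.

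**Conclusion.** The point holds as a minor mismatch between a stated criterion and its stated purpose. Focus groups are the one named source for appropriateness, practicality and acceptability, and the data are meant to improve the intervention. The theme criterion, read as written, would leave out barriers voiced by only some participants.

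Its size cannot be derived from the article. The probabilities above show how strict a literal reading would be under assumed prevalences and independence; they do not estimate what will be lost. The conclusion rests on taking the sentence at its word. If the authors meant shared themes in a looser sense, the defect is one of wording, and the same correction settles it.

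The go/no-go decision is not affected, because the three progression criteria concern adverse events, recruitment and retention. What is affected is how completely the qualitative findings inform the redesign.

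**What to change.** In Qualitative data analysis, replace the condition that meanings be shared by everyone with wording such as: *themes and subthemes will be derived from all views expressed, including minority and contradicting views, with an indication of how widely each was raised (for example, in how many focus groups).*

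The cost is slightly more analysis and reporting work. Randomisation, sample size, data collection and the quantitative analysis are unchanged.

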### Data storage and protection

Research data will be kept for 10 years in line with UK data protection regulations [71]. Physical data will be pseudo-anonymised with a unique ID number and stored confidentially in locked filing cabinets/on password-protected university computers accessible only to the research team. Digitally recorded interview transcripts will be stored securely on a password-protected computer that only the researchers will have access to. Audio recordings will be destroyed after the recordings are transcribed verbatim.

## Discussion

This study will explore the feasibility and acceptability of the Physical Activity Intervention for Loneliness (PAIL) in community-dwelling older adults. The key features of the study are based on effective components of physical activity interventions to treat loneliness obtained from a systematic review and meta-analysis of the existing evidence that highlighted the lack of physical activity interventions for older adults residing in community settings [23]. Studies to date either included non-PA interventions only or mixed design studies for only one or two outcomes (e.g. RCTs, case-control studies, longitudinal). The randomised controlled design of this feasibility study allows improvement upon the methodological rigour of the current evidence. Consequently, this feasibility study uses objective measures of PA and comprehensive methods of assessment of social health which will allow estimation of the mechanisms of association between PA and social health outcomes in older adults in the future large-scale study. Findings from this study will be of the interest to healthcare professionals and community organisations working with older adults at risk of loneliness or social isolation in the implementation of exercise interventions to address this problem in society.

### Dissemination

Dissemination will include a summary of the results for participants, publication of an open-access article detailing the full findings (also part of the PhD student’s thesis) and presentation of study findings at conferences. The results of this feasibility study will be used to inform the development of a large-scale RCT. Participants in the intervention will be sent a feedback information sheet with the results of the study by e-mail or post (if no e-mail is available). The findings are also intended to be disseminated at the British Geriatric Society Loneliness annual meetings and via news at www.campaigntoendloneliness.org. The published study protocol and journal paper will be uploaded to the Current Research Information System (CRIS) – PURE portal available at pure.bham.ac.uk open to the academic staff, students and external researchers.

### Trial status

This feasibility trial is registered at Clinicaltrials.gov Identifier: NCT03458793. Ethical approval for the project was received from the STEM Research Ethics Committee of the University of Birmingham, UK (ERN_16-1419A). Participant recruitment and baseline data collection started in October 2017 and is expected to be finished by November 2018. The study will be fully completed by May 2019.

## Abbreviations

ANOVA: Repeated-measures analysis of variance
BMI: Body mass index
BP rest: Resting blood pressure
BVSC: Birmingham Voluntary Service Council
EE: Energy expenditure
ES: Effect size
GP: General practitioner
HADS: Hospital Anxiety and Depression Scale
HR_max_: Heart rate maximum
LSNS-6: 6-Item Lubben’s Social Network Scale
M: Means
MET: Metabolic equivalent
MOCA: Montreal Cognitive Assessment
MOSSSS: Medical Outcomes Study Social Support Survey
*N*: Number
PA: Physical activity
PAIL: Physical Activity Intervention for Loneliness
RCT: Randomised controlled trial
RPE: Borg’s Ratings of Perceived Exertions
SD: Standard deviations
SEE: Self-efficacy for exercise scale
SPPB: Short Physical Performance Battery
STEM Ethical Review Committee: Science, Technology, Engineering and Mathematics Ethical Review Committee
UCLA-8: 8-Item The University of California, Los Angeles Loneliness Scale
WLC group: Wait-list control group
